## Methods

We employ a quasi-experimental nursing-led intervention trial with a repeated measures design [36] based on a convenience sample of four nursing home clusters and a total sample of 411 dementia patients. All dementia patients in the comparison group will be obtained from the Zurich Life And Death with Advanced Dementia (ZULIDAD) Study [37]. The ZULIDAD data were collected from people with dementia (men and women), who are older than 70 years in one nursing home (*n* = 150), in 2015. Data between intervention sites and comparison site are similar because the same assessment instruments were used, based on an older person assessment instrument, and include pain duration, pain intensity, behavioural problems, differences of psychopharmacological drugs, and differences of analgesics. The comparison can be made with data from the first day and from the 49^th^ of each data collection phase (t0, t1, t2) and with a historical sample of pain duration and pain intensity from the last pain assessment documented in the older person Assessment Instrument Data (RAI) of each participant.

People with dementia in the intervention group will be are recruited in three healthcare institutions in the cantons of Thurgau and Zurich.

All healthcare workers from these three intervention institutions are included in the study, trained and coached in the provision of interventions. The following inclusion criteria apply to healthcare workers:must be at least 18 years old;must have been employed at least 12 months in the respective organisation;must work for at least 30% of a working week;be able to communicate in German.

The collection of data will take place in three nursing homes in the Canton of Thurgau and in the Canton of Zurich. For the comparison group, data from the ZULIDAD study [37] will be used.

All older people are screened for eligibility to participate in the study. Recruitment is described in Fig. 1. Only older people with documented nursing-initial-assessment symptoms of dementia are included in this intervention trial by author no. 3.

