Sustainability and veracity of the interventions are ensured by following the comprehensive evaluation process based on Dobbins [45] that consists of:assessment of the accuracy between the conducted intervention and the study protocol: 50% of the intervention protocols are tested for compliance with the study protocol based on selected pain management strategies and structured communication skills (ISBAR, SOPIER, prompt initiation of medical prescriptions, usage of non-analgesic pain management strategies) by descriptive analysis.evaluation of operating procedures that are associated with pain managementquestioning of acceptability of the interventions carried out for all health care workers with a scale from 0 (= no acceptance) to 10 (= fully accepted)compliance (adherence) of interventions for all health care workers with a scale from 0 (= no adherence) to 10 (= complete adherence)assessment of the potential for change in clinical practice among healthcare workers with a scale from 0 (= no conversion potential) to 10 (= complete transformation possible)assessment of potential change in the management of pain among health care workers with a scale from 0 (= no change in potential) to 10 (= comprehensive amendment potential)

Pain as primary outcome is measured in all people with dementia in the comparison and intervention groups by means of:pain events per shift and per week;degree of pain intensity per work shift, per week day;pain-free intervals.

Secondary outcome variables will be measured by:frequency of behavioural problems (Neuropsychiatric Inventory NPI [46]);number/dosages of psychotropic drugs;Number/dosages of analgesics.

The documentation regarding the assessment of pain by nurses is always done in duplicate, by a health care worker on different education level. Tertiary outcome variables will be measured by:changes in the assessment of pain by healthcare worker on healthcare assistant level andchanges between the two healthcare worker groups on healthcare assistant level and registered nurse level.

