Multilevel analyses (linear mixed models): The required number of cases for basic evaluations using multilevel models/linear mixed models have been determined by the approximation method [47] - with equal power and significance level as in the event analyses. This approach recognises a random intercept model with covariates that only vary between older people (treatment). In order to carry out only two repeated measurements per person, approximately *n* = 47 persons are required using a regression coefficient of 1 and a standard deviation of 0.5.

There are three data monitoring cycles (T0, T1, T2) and two intervention cycles (I1, I2) to measure the primary and secondary outcomes, see Fig. 3. Each data monitoring cycle extends over 7 weeks (=49 days) and includes seven different weekdays and at least three different work shifts. The data are extracted from the older people’ specific pain diaries (degree of pain intensity), which are kept separately from conventional nursing documentation. For the description of the sample, socio-demographic data on age and gender are collected from all participants. Additional data on qualifications and professional experience are collected from nursing staff, and care needs, dementia type and severity of dementia from people with dementia.

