**Fig. 3 Fig3:**
[figure not shown]
Time schedule

The actual data collection will be done by a study nurse with a BSc in Nursing. Potential confusions/problems with the raw data are discussed within the respective healthcare institution and with the leader of the study. Ambiguities with the procedure of data collection are discussed with the head of project management within the research team who also keeps a research diary. The study nurse transfers the anonymised data to the project management after the third measuring cycle. Two other study nurses enter the data into SPSS and carry out data cleansing before proceeding with the data analysis. The data of the comparison group are disclosed to the project management “PID” in encrypted form by the project manager “ZULIDAD”.

Data analysis will be performed using the IBM software programme SPSS® (version 24). The socio-demographic data are analysed descriptively (frequencies, central tendencies, standard deviations) and the outcome variables as follows:Pain intensity, duration and pain-free intervals are investigated in all dementia patients of the comparison and intervention group measuring the average duration of pain events per work shift (each work shift lasts 8.25 h) and per weekday, and the average degree of pain intensity per work shift, per work day as well as the duration of pain-free intervals with multilevel and events history analyses based on the data observation intervals T0, T1, T2.For the multilevel analyses (linear mixed models) over time, two levels are considered: the dementia patient and the healthcare institution. The event history analyses use cluster-adjusted Cox regressions. Furthermore, event history analyses will focus on evaluating the influence of the two nursing professional groups (at assistant/secondary and tertiary level), the pain pharmacotherapy (number and dosage), behavioural problems (NPI) and the psychopharmacotherapy (number and dosage).

A change in the assessment of pain by the healthcare workers is checked with interrater reliability tests. By means of the interrater reliability test, a potential variation between the two nursing groups on assistant/secondary and tertiary level is monitored.

To ensure the quality of data analyses, each data analysis step is independently checked by three different people.

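### The pain data described for the historical comparison group cannot support between-group tests of pain events (Ha1) and pain-free intervals (Ha3), and leave the basis of between-group Ha2 unclear

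*Protocol article*

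**What the plan says.** All references are to the Protocol article, Methods.

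- **Comparison group.** All comparison residents come from the Zurich Life And Death with Advanced Dementia (ZULIDAD) study: people with dementia "who are older than 70 years in one nursing home (*n* = 150), in 2015".
- **Shared variables.** The same paragraph asserts that "Data between intervention sites and comparison site are similar because the same assessment instruments were used". The pain variables it lists are duration and intensity.
- **Time points.** The next sentence has two halves. The first reads "The comparison can be made with data from the first day and from the 49^th^ of each data collection phase (t0, t1, t2". The second adds a "historical sample of pain duration and pain intensity from the last pain assessment documented in the older person Assessment Instrument Data (RAI", for each participant. Neither half says which group supplies which data.
- **Outcomes (after Fig. 2).** "Pain as primary outcome is measured in all people with dementia in the comparison and intervention groups", by events per shift and per week, intensity per shift, and pain-free intervals.
- **Hypotheses.** Ha1 (events), Ha2 (intensity) and Ha3 (pain-free intervals) are each worded both as before/after and as between-group.
- **Data source (before Fig. 3).** Trial data are extracted from "specific pain diaries (degree of pain intensity), which are kept separately from conventional nursing documentation", over cycles of 49 days with at least three different work shifts.
- **Analysis (after Fig. 3).** Pain-free intervals, along with the intensity of pain and how long it lasts, "are investigated in all dementia patients of the comparison and intervention group measuring the average duration of pain events per work shift", using T0, T1 and T2.

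**The concern.** The paragraph on the comparison group and the paragraphs on outcomes, hypotheses and analysis describe different data for the same 150 residents. The first describes a finished historical data set with two pain variables and a last routine assessment. The others assume that those residents have shift-level records across the trial's own monitoring cycles.

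Two things are at stake. First, an outcome that one group does not have cannot be compared between groups, whatever model is used. Second, where both groups do have an outcome (intensity), the comparison is fair only if the values arise in the same way. Intervention 1 sets out to change how staff assess pain. If ratings from dedicated diaries are set against a routine record from another home, part or all of an apparent effect could come from how pain was recorded.

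**Working it through.** **1. The plan's own figure.** The event-history calculation gives 121 events and 179 persons. With hazard ratio 0.6, covariate SD 0.5, two-sided 0.05 and power 0.8:

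- events = (1.960 + 0.842)² / (0.5² × ln(0.6)²) = 7.849 / (0.25 × 0.2609) = 120.3, rounded up to 121;
- persons = 120.3 / 0.75 = 160.4, rounded up to 161; 161 / 0.9 = 178.9, rounded up to 179.

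The figure reproduces, and nothing here turns on an error in it. It does show that the Cox analysis needs observed event times. A group without event times adds nothing to a between-group coefficient in that model.

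**2. What each outcome needs, and what the comparison group is said to hold.**

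| Hypothesis | Needed in both groups | Described for the comparison group |
|---|---|---|
| Ha1 | pain events per shift and per week | not among the listed variables |
| Ha2 | intensity per shift | intensity listed; the source named is the last RAI assessment |
| Ha3 | length of pain-free intervals | not among the listed variables |

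**3. Can the comparison group have T0, T1 and T2?** These are the trial's own monitoring cycles around its two interventions. The Methods place data collection in the three intervention homes. They say the comparison data are passed on in encrypted form by the ZULIDAD project manager. Data collected in 2015 cannot have been recorded in the trial's cycles, and no passage maps them onto those cycles. No passage says that the comparison home kept pain diaries.

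**4. Density of data.** Inputs: 49 days per cycle, three cycles, and an assumed three shifts a day (at 8.25 h each, 3 × 8.25 = 24.75 h, enough to cover a day).

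- Diary slots per resident: 3 × 49 = 147 per cycle; 147 × 3 = 441 in all.
- Days 1 and 49 only: 3 × 2 = 6 per cycle; 6 × 3 = 18 in all; 18 / 441 = 4.1%. The share is 2/49 for any number of shifts a day.
- Last RAI record: one value.

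**5. What follows under each reading.**

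- *Last RAI record only.* One value gives no event count per shift or week, no event time and no pain-free interval.
- *Day 1 and day 49 also available.* These days fall in weeks 1 and 7, so no week is observed in full and the 47 days between are unseen. Weekly counts cannot be formed, and neither can the length of pain-free intervals over a cycle. At most, events per shift on those two days could be compared, and only if events were recorded at all.
- *RAI taken in both groups.* Intensity and duration can be compared on one source. The outcome and analysis paragraphs, however, specify per-shift measures, which in the trial come from the diaries.

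**6. Intensity: which differences are stated.** The source differs (diary against RAI), and so does the density (shift level against a last assessment). In the trial, assessments are made in duplicate by workers of different education levels, and Intervention 1 trains and coaches staff on the BESD. Nothing of the kind is described for the comparison home. The scale used in the diary is not named.

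**The case against.** The strongest case on the other side is that the text is ambiguous rather than wrong.

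- The sentence with the RAI value also names t0, t1 and t2, and the words for each participant may cover both groups.
- The outcome and analysis paragraphs state outright that the comparison group has these measures.
- The Background names pain intensity and pain duration as the primary outcomes, which are exactly the two shared variables.
- The figures and the comparison study's own protocol are not at hand.

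Much of this stands, and it rules out three stronger readings that a reader might infer:

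- *The comparison group has nothing but one RAI value.* This is the most natural reading, but it is an inference. The text does not say that other records are absent.
- *Ha2 compares two different scales.* This is not shown. A diary is a recording medium, the BESD appears as training content, and the article asserts common instruments. If T0 precedes Intervention 1, as the before/after hypotheses imply, the T0 ratings also predate the trial's training.
- *No group-by-time term can be estimated for any primary outcome.* This would need the first reading to be certain.

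The size of any bias in Ha2 cannot be given either, since the article states no diary scale and documents no offset between sources.

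The objection does not remove the contradiction. Even the generous readings leave weekly events and pain-free intervals without comparison data. Nor is this detail that a fuller document would be expected to carry: the data source and the primary outcomes are both stated here, and they do not fit together.

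**Conclusion.** The point holds as an unreconciled contradiction within the Methods. On the data described, the between-group parts of Ha1 and Ha3 cannot be computed: two of the three between-group primary hypotheses. The between-group part of Ha2 can be computed, but as diary against RAI it would be open to confounding by source, recording density and rater training. The within-group before/after parts of all three hypotheses are unaffected.

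This rests on two assumptions: that the list of shared pain variables is complete, and that the trial's cycles were not mirrored in the 2015 data. If the authors can show equivalent shift-level comparison data, the conclusion on Ha1 and Ha3 falls away. The need to state the source remains.

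**What to change.** 1. In the paragraph on the comparison group, state which pain data, which instrument and which time points that group holds, and which group supplies the day 1, day 49 and last-RAI values.
2. In the outcomes, hypotheses and analysis paragraphs, limit between-group comparisons to outcomes that both groups have from the same source. Analyse pain events and pain-free intervals within the intervention homes only, unless equivalent comparison data are shown to exist.
3. Compare intensity and duration between groups using RAI items in both. Keep the diary values for the within-group analysis, and do not set them against RAI values.
4. Qualify the statement on common instruments so that it covers only the data for which it is true.

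The cost is amended wording and extraction of RAI pain items for the intervention residents. The Methods speak of RAI assessments documented for each participant, so these should be available if that phrase covers both groups. The price is that up to two of the three between-group primary hypotheses become within-group only, and the between-group comparison of intensity gives up the finer detail of the diaries.

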## Background

Approximately 25% of people over the age of 85 years in Switzerland live in retirement and nursing homes. The average length of stay is 2.6 years [1]. More than half the people in nursing homes live with symptoms of dementia or have been diagnosed with dementia [2]. People with dementia show the characteristic symptom manifestation: 1) shortness of breath often combined with respiratory infections leading to pneumonia; 2) pain and 3) behavioural disorders, in particular agitation, restlessness and disorientation [3–13].

Of those people with dementia, 19–83% suffer from pain [7, 8, 10, 14–16] that is inadequately treated in the last months of life [17, 18]. The Pallhome study conducted in Switzerland identified pain and behavioural problems, as causing the greatest difficulties in controlling symptoms in dementia patients in nursing homes [19]. However, the fact that both symptoms can occur simultaneously makes it difficult to differentiate them [20, 21]. Zwakhalen and colleagues [14] also detected an increased risk of pain for people with multiple concurrent health problems and for people taking several analgesics. Both factors are true for people suffering from dementia in nursing homes. Untreated pain can lead to depression, sleep disorders, falls, malnutrition and deterioration in daily activities and physical functions [22]. In this context, various barriers to the treatment of pain in people with dementia have been identified [23–27] including: inadequate knowledge about the relationship between pain and behaviour; interpretation of behaviour; intensity of pain; pharmacological interventions and their side effects; non-pharmacological interventions; and interventions without prior clinical assessment by professionals. In addition, organisational frameworks such as the definition of responsibilities, the physicians’ claim that the patient had no pain and high staff turnover have been identified as barriers relevant to effective pain management [23, 25–28].

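### The historical pain value is each participant's last documented RAI assessment with no index date, while study values fall on set days, so the time points of the between-group comparison are not aligned

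*Protocol article*

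**What the plan says.** All of this stands in the Protocol article, Methods, unless noted.

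- The comparison residents come from the "Zurich Life And Death with Advanced Dementia (ZULIDAD) Study". They are people with dementia "older than 70 years in one nursing home (*n* = 150), in 2015".
- The study data for the comparison are taken "from the first day and from the 49^th^ of each data collection phase (t0, t1, t2").
- The same sentence adds a historical sample of pain duration and pain intensity, taken "from the last pain assessment documented in the older person Assessment Instrument Data (RAI) of each participant". It gives no index date, window or cut-off for the last assessment.
- Comparability rests on one argument: "Data between intervention sites and comparison site are similar because the same assessment instruments were used".
- Each of the three primary hypotheses (H_a1 to H_a3) includes a contrast between intervention and comparison groups as well as a contrast over time.
- The Background says that people with dementia have pain "that is inadequately treated in the last months of life" and gives an average nursing-home stay of 2.6 years.

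**The concern.** The two rules select records differently. A value on a set study day exists only if the resident is alive and in the home on that day, and the choice of day does not depend on what happens to that resident later. A last-record rule runs to the end of whatever record exists. For someone who has left, that end is set by the exit.

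Using the same instrument in both groups does not remove this difference, because it concerns when pain was rated and not how. If recorded pain rises towards the end of life, the rule raises the comparison value. Deaths during the 425 days also remove intervention residents before T1 and T2. Both effects would then make the intervention look better without any effect of the training, in a contrast that belongs to every primary hypothesis.

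**Working it through.** **Figures in the plan.** The document gives no figure for this point. Its Cox sample size reproduces: (1.960 + 0.842)² / (0.25 × ln(0.6)²) = 120.3, so 121 events; 120.3 / 0.75 = 160.4, so 161; 161 / 0.9 = 178.9, so 179 people. That calculation has no bearing on when pain is measured.

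**What each reading of the last record implies.**

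| Reading | Comparison residents who left | Consequence |
|---|---|---|
| Last before death or discharge | Final record before exit | Not aligned with set days |
| Last in 2015, or last at data extraction | Still the final record before exit, for those who left before the cut-off | Partly not aligned |
| As above, with exited residents excluded or none | Not present | No bias from this source |
| Each participant includes intervention residents | Same rule in both groups | For intervention residents the value may fall before, during or after the training |

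An index date is needed under every reading. The bias from exits vanishes only in the third row, and the document does not say that this row applies.

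**Illustration of size.** Inputs:
- Mean stay 2.6 years (Background, for nursing homes in general). A constant exit rate and a one-year window are assumptions.
- Pain prevalence 60% near exit and 40% otherwise: assumptions. The 19-83% range in the Background does not separate end-of-life pain from earlier pain, so it does not support this split.
- Every exit is counted as a record near the end of life. This is generous, since some residents are discharged and a periodic record may precede death by months.

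Comparison group:
- Share exiting in one year: 1 − exp(−1/2.6) = 0.319.
- Prevalence in last records: 0.319 × 0.60 + 0.681 × 0.40 = 0.464.

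Intervention group on a set day:
- Nobody near exit: 0.40. Spurious reduction 1 − 0.40/0.464 = 13.8%.
- Near exit means exit within 3 months: 1 − exp(−0.25/2.6) = 0.092; prevalence 0.40 + 0.20 × 0.092 = 0.418; reduction 1 − 0.418/0.464 = 9.9%.
- Near exit means exit within 6 months: 1 − exp(−0.5/2.6) = 0.175; prevalence 0.40 + 0.20 × 0.175 = 0.435; reduction 1 − 0.435/0.464 = 6.3%.

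The range is about 6-14%. The upper end treats no intervention resident as near exit on a set day, which is unrealistic.

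**The same on a continuous scale.** Let f be the excess share of near-exit values in the comparison group and d the extra pain near exit in SD units. The contrast shifts by f × d. Take d = 0.5 (assumed), 150 comparison and 411 − 150 = 261 intervention residents, and ignore clustering, so SE = √(1/150 + 1/261) = 0.102 SD.

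| f | Shift (SD) | Rejection rate of a two-sided 5% test, no true effect |
|---|---|---|
| 0 | 0 | 5% |
| 0.10 | 0.05 | 8% |
| 0.25 | 0.125 | 23% |
| 0.50 | 0.25 | 68% |

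The prevalence illustration has excess shares from 0.319 − 0.175 = 0.144 to 0.319, which lie within this table.

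**The case against.** A reader might infer that the comparison is one of end-of-life pain against pain in survivors, with the last record fixed by death or departure. The document does not support that. It reports no deaths or exits in the comparison data, it says the data were collected in 2015, and the cohort's name is weak evidence of how many residents had died. Many could have been alive at their last record. This stands, and it is why the point is conditional.

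The phrase about each participant may also cover intervention residents. That would remove part of the asymmetry but would leave their value undated relative to the training.

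The direction is not established either. The Background says that pain is inadequately treated in the last months, not that recorded pain is higher then. The Methods warn that a zero BESD score does not rule out pain when no pain behaviour is visible. If pain is less visible near death, the bias shrinks or reverses.

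The text says only that the comparison can be made in this way, and the analysis paragraph describes shift-level outcomes over T0, T1 and T2 for both groups. So the RAI value is not shown to be the sole primary value. It is still the only stated source of historical pain duration and intensity.

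Finally, a condensed article may leave extraction windows to the full protocol. That would answer a complaint about missing detail. Here the article does state a rule, and the rule itself is the weakness.

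**Conclusion.** The point holds in a limited form. The historical value is undated and selected as the last on record, the study values are tied to set days, and shared instruments do not align them. For any comparison resident who left before the cut-off and is kept in the data, the value is a final pre-exit record. If recorded pain is higher near the end of life, the contrast is biased in favour of the intervention.

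The size is unknown. The 6-14% rests on the assumed 60%/40% prevalences, a constant exit rate with a 2.6-year mean stay, and a one-year window. With no exited residents in the data it is zero.

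It may be tempting to set this figure against the 20% in H_a1, but that does not follow. H_a1 concerns pain events, the RAI sample supplies duration and intensity, and the illustration uses prevalence, which is the outcome of none of the three primary hypotheses. The change is worth making because it is cheap and the contrast is a primary one, not because a large bias has been shown.

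**What to change.** In the Methods paragraph on the comparison group, replace the last RAI assessment by the one closest to a fixed index date, chosen without regard to later death or exit. An example is the first assessment after entry into the 2015 data. Apply the same rule to intervention residents, using the RAI record nearest the start of T0, and state that the rule covers both groups.

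The cost is a changed extraction rule, set before the comparison data are disclosed to the project. Some residents may lack a dated record near the index date, and the change is possible only if the comparison study holds dated RAI records, which the document does not say.

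### The text gives intervention and comparison residents different entry rules, and no stated analysis step handles age or dementia severity in the between-group contrasts

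*Protocol article*

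**What the plan says.** All of this is in the Methods section of the protocol article.

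- **Comparison group.** "All dementia patients in the comparison group will be obtained from the Zurich Life And Death with Advanced Dementia (ZULIDAD) Study". Its 150 residents are described as people with dementia "who are older than 70 years in one nursing home", with data from 2015.
- **Intervention group.** Residents are "recruited in three healthcare institutions in the cantons of Thurgau and Zurich". The one criterion for residents in the text is "Only older people with documented nursing-initial-assessment symptoms of dementia are included in this intervention trial". Recruitment is referred to Fig. 1, which is not shown.
- **Ground for comparability.** "Data between intervention sites and comparison site are similar because the same assessment instruments were used". The sentence goes on to list pain, behaviour and drug variables. Age and dementia severity are not in that list.
- **Use of the contrast.** H_a1, H_a2 and H_a3 each combine a before-after part with an intervention-versus-comparison part.
- **Age and severity.** The paragraph on the data monitoring cycles collects age and gender to describe the sample. As additional data it collects "care needs, dementia type and severity of dementia from people with dementia".
- **Analysis.** The mixed models have two levels, resident and institution. The event history analyses are cluster-adjusted Cox regressions, and the factors named for them are staff group, analgesics, NPI and psychotropic drugs.

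**The concern.** In a non-randomised comparison with historical controls, the groups are only as comparable as their entry rules and the adjustment make them. Here the stated rules differ: one side has an age floor and comes from a study whose name refers to advanced disease, while the other side has neither in the text. Age and stage can plausibly affect how much pain residents have, how visible it is on an observational scale, and what analgesics they receive. The article itself warns that a BESD score of zero does not rule out pain in someone who shows no pain behaviour.

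The only argument for similarity concerns the instruments. Two groups measured with the same instrument can still be different kinds of resident. If they are, a between-group difference, or the lack of one, could come partly from who was admitted to each group. All three primary hypotheses use that contrast.

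**Working it through.** **1. Entry rules side by side (Methods).**

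| | Comparison | Intervention |
|---|---|---|
| Source | One home, 2015 data | Three institutions |
| Residents | 150 | 411 − 150 = 261 |
| Age | Older than 70 | Older people, no cut-off stated |
| Dementia | Study named for advanced dementia; described in the text only as people with dementia | Symptoms documented in the nursing initial assessment |
| Severity limit | Not stated (entry rule not shown) | Not stated (Fig. 1 not shown) |

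The age difference is explicit: on the text, a resident aged 70 or younger could enter the intervention group but not the comparison group. The severity difference is suggested by the study's name and is not stated as a rule.

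**2. Does a stated analysis step deal with it?** Age is descriptive. Severity is collected but given no role. The institution level cannot remove the mismatch, because the single comparison home is the whole comparison group. The sample-size paragraph mentions other covariates in the Cox model without naming them.

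**3. The plan's own figure.** The Cox calculation uses HR 0.6, covariate SD 0.5, two-sided alpha 0.05 and power 0.8:

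events = (1.960 + 0.842)² / (0.5² × (ln 0.6)²) = 120.3, so 121, as stated.

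Persons = 121 / 0.75 = 161.3, so 162. Adding 10% gives 162 × 1.1 = 178.2, so 179, as stated. (Dividing by 0.9 gives 180, which is immaterial here.) The sample size is not in question. It protects against chance error and does nothing against case mix.

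**4. Illustration of sensitivity.** The case-mix gaps below are assumptions, as the document gives none. Take no true intervention effect, 150 versus 261 residents, no clustering, no adjustment, and a contrast of levels.

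SE in SD units = √(1/150 + 1/261) = 0.1025.

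P(p<0.05) = Φ(d/SE − 1.96) + Φ(−d/SE − 1.96).

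| Assumed gap d (SD) | Chance of p<0.05 |
|---|---|
| 0.1 | 16% |
| 0.2 | 50% |
| 0.3 | 83% |
| 0.5 | >99% |

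For the Cox model, the comparison share is 150/411 = 0.365 and about 0.75 × 411 × 0.9 = 277 events are expected. The standardised shift is √(277 × 0.365 × 0.635) × |ln HR|. An assumed case-mix hazard ratio of 0.9, 0.8 or 0.7 gives p<0.05 with probability 14%, 43% or 82%. With 121 events the figures are 9%, 22% and 47%.

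These figures show that modest gaps would matter if present. They do not show that such gaps exist.

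**The case against.** The strongest reply is that much of the mismatch is inferred. Four stronger readings are tempting, and the document does not support them.

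- **That a resident with mild dementia could not have been a control.** The word advanced appears only in the source study's name, and the text describes those residents simply as people with dementia over 70. Lack of overlap on stage is therefore not shown, nor is the claim that regression would have to extrapolate across stages. Only the age floor is explicit, and few nursing home residents may fall below it.
- **That dementia symptoms are the sole intervention criterion.** The sentence makes them necessary. Fig. 1 or the full protocol may add limits.
- **That a resident whose dementia appeared after admission is excluded.** This follows only if the nursing initial assessment is fixed at admission and never updated, which the text does not say.
- **That the bias rivals the hypothesised 20% effects of H_a1 and H_a3.** No stage mix or pain difference by stage is given, so no percentage shift can be defended. H_a2 posits 50%.

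Two further replies have weight. If the contrast is a change from T0, a stable offset in level would largely cancel. That requires similar trends across ages and stages, and control data that yield a change; Methods also mentions a historical sample from the last documented pain assessment. Second, the similarity sentence can be read as being about measurement only. On that reading the article gives no argument at all that the residents are comparable.

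It is also fair that the design is openly quasi-experimental with historical controls, and that covariates may be named in an analysis plan not shown. What stands is that the stated entry rules differ and that nothing stated handles the difference.

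**Conclusion.** The point holds in limited form. The text defines the two groups by different entry rules, supports their similarity only by shared instruments, and gives age and severity no role in the between-group analysis. The intervention-versus-comparison parts of H_a1 to H_a3 may therefore partly reflect case mix. Size and direction cannot be computed from the document; the illustrative probabilities rest on assumed gaps and on an unadjusted contrast of levels without clustering. The before-after contrast within the intervention homes does not use the comparison residents and is not affected. This is a cheap improvement, not a defect that must be repaired before the trial can be interpreted.

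**What to change.** 1. Restrict every intervention-versus-comparison contrast to residents older than 70. Where ZULIDAD holds a comparable severity measure, restrict also to the severity range present in both groups, and adjust for baseline age and severity within it.
2. Keep all intervention residents for the before-after contrast.
3. Replace the instrument-based similarity statement with a table of age and severity by group.
4. If ZULIDAD severity is not on a comparable scale, apply the age restriction alone and rest the main inference on the before-after contrast.

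**Cost.** Wording, a filter and two covariates on the intervention side, where age and severity are already collected. On the comparison side the severity measure must be checked, because it is not among the shared variables listed. The between-group contrast will use fewer intervention residents, and possibly fewer controls, and will apply more narrowly. The number lost is unknown. As a guide, if 111 of the 261 intervention residents fell outside the common range and all 150 controls stayed, 300 would remain, against the 179 in the plan's own Cox calculation, before any allowance for clustering.
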